### Safety reporting

Any spontaneously reported unfavorable symptom that develops or deteriorates during the study will be classified as an adverse event (AE), whether or not it is considered to be related to the study treatment. AEs comprise exacerbation of pre-existing symptoms, increase in frequency or intensity of a pre-existing episodic event or condition, condition that is detected after trial intervention administration, and continuous persistent illness or a symptom present at baseline that expectedly or unexpectedly worsens following administration of the intervention. Serious adverse events (SAEs) are those considered to be potentially or actually resulting in death, in significant or persistent incapacity/disability, or requiring new or prolonged inpatient hospitalization. The trial team member becoming aware of the AE must record it. The AE is then reviewed by the trial manager and reported to the principal investigator within 72 h to assess causality. In any case of a SAE, the trial manager must be notified within one working day by the member of the trial team becoming aware of the event. The trial manager is required to notify the principal investigator within one working day. The principal investigator is responsible for reporting fatal and life-threatening serious adverse reactions to the competent authorities within 7 days of becoming aware of the event. If necessary due to an adverse event, participants are referred to an inpatient clinic in case of extreme symptom deterioration or substantial risk of harm to self/others by their trial therapist. The trial will be stopped by the principal investigator in case that the rate of AEs attributable to “Goals in Focus” exceeds 30%. Study and treatment participation can be terminated either by the participants themselves at any given time and without justification or by the principal investigator in case of significant harm for the participant. Excluded participants are offered regular treatment at our outpatient clinic. As the trial manager continuously tracks the number of AEs and SAEs throughout the study, no interim safety analysis is planned. The principal investigator and the trial manager have access to the safety data at any given time and will make it available for responsible authorities upon request.

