We argue that each of these factors contributes to the observed difficulties of patients with negative symptoms in pursuing personally meaningful goals. It follows that interventions that specifically target these factors are likely to be more successful in reducing motivational negative symptoms than less specific interventions, such as behavioral activation and cognitive therapy. Given that each of these factors is associated with negative symptoms but none of them can fully account for negative symptoms, we also expect approaches addressing several of these factors to be superior to interventions that focus on a single factor. This expectation is corroborated by the fact that approaches that have targeted several of these factors, e.g., by combining cognitive interventions with social skills training [64] or with interventions targeting anhedonia [65-67], tend to produce more promising effects. In addition, given that the factors driving amotivation might vary between patients, we argue that intervention approaches will more likely be effective if their focus can be flexibly adjusted to the individual needs of a given patient [21]. However, to our knowledge, there is no approach that addresses the full range of relevant mechanisms in a customizable manner.

On that account, we developed a novel comprehensive, individualized cognitive behavioral outpatient intervention (“Goals in Focus”) that supports patients in specifying attainable personal goals and overcoming obstacles in goal pursuit. The intervention aims at supporting patients to realize personally meaningful goals by addressing reward processing, anticipatory pleasure, demotivating beliefs, and social and problem-solving skills.

With this feasibility trial, we aim to test the feasibility (i.e., referrals, eligibility rate, number of consenting participants, retention rate, attendance rate, dose of intervention, data attrition, and treatment adherence) and acceptability (i.e., drop-out rate, number of adverse events, participants’ and therapists’ satisfaction) of the therapy manual and trial procedures as well as to obtain first estimates of the effect size that can be expected from “Goals in Focus” (i.e., extent of change in motivational negative symptoms as primary outcome) to inform the sample size calculation for a fully powered clinical trial.

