Blinding of participants is not possible due to the nature of this study. Because trial raters work in the same facilities as trial therapists (i.e., they attend weekly team meetings, meet patients on the hallway, etc.), they also cannot be reliably blinded. Therefore, each assessment is video-recorded and rated by an independent second rater blinded to group allocation and time of assessment. At the beginning of each assessment, participants are reminded to not disclose their group allocation. Video sequences that could reveal the participant’s allocation or point of assessment are deleted before the secondary rating. Secondary raters are asked to record any breaks of blinding, even if the break is equivocal. Putatively unblinded raters are asked to guess the allocation group for the respective participant. Confirmed breaks in blinding of raters follow a standard operating procedure to maintain blind outcome assessments by reallocating “blind” raters for the respective secondary rating, therefore not biasing results.

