#### Sample size

An a priori power calculation is not appropriate for this feasibility trial as the study aim is not to test efficacy. Nonetheless, we aim to examine first effect size estimates of “Goals in Focus” on our primary and secondary outcomes. These estimates will inform the sample size calculation for a future fully powered RCT. Based on the recommendations for feasibility studies [75] and on existing feasibility trials in this field [76, 77], the target for this feasibility study was set at *N* = 30 participants (*n* = 15 intervention group; *n* = 15 wait-list control group).

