#### Wait-list control group

Participants randomized to the “wait-list control group” will be contacted again after 6 months for post-assessment and then offered the “Goals in Focus” intervention. These participants will also be informed that they may use other pharmacological or psychosocial mental health care services but are asked to refrain from psychological interventions that directly target motivational negative symptoms. At the end of the wait-list period, participants in this condition are asked to provide information on any inpatient or outpatient treatment they have received and on major events they consider to have influenced their symptoms during this period.

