#### Goals in Focus

Participants randomized to the “intervention group” will receive up to 24 weekly 50-min sessions of “Goals in Focus” within the following 6 months. The main components of “Goals in Focus” were selected based on basic research [21] and existing therapy approaches on motivational negative symptoms [47, 66, 74, 78]. They were then combined to a customized and readily conveyable manualized approach. “Goals in Focus” follows cognitive–behavioral principles and aims to alleviate motivational negative symptoms by improving goal pursuit. The intervention is delivered in a one-to-one setting by clinical psychologists (master’s degree plus advanced or completed clinical training). All trial therapists receive an additional 2-day training in using the treatment manual, including background information on the rational of “Goals in Focus” and a step-by-step introduction to the individual intervention components. Trial therapists are offered weekly supervision by a senior expert on cognitive behavior therapy for psychosis and are requested to attend at least once per month to increase adherence to the treatment manual. “Goals in Focus” comprises four main phases: (1) preparation, (2) goal setting, (3) supported goal pursuit, and (4) working towards autonomous goal pursuit. An overview on the structure and sequence of “Goals in Focus” intervention is presented in Fig. 2, a table on the domains and intervention elements of “Goals in Focus” is provided in supplement S2.

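### Adverse events are captured by spontaneous report with unequal described contact by arm: label the counts non-comparable between arms and add a common question at t1

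*Protocol article*

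**What the plan says.** All references are to the protocol article.

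- **Capture (Safety reporting).** The rule is "Any spontaneously reported unfavorable symptom that develops or deteriorates during the study will be classified as an adverse event (AE"), whether or not it is thought related to treatment. On recording: "The trial team member becoming aware of the AE must record it".
- **Contact, intervention arm (Goals in Focus).** Participants receive "up to 24 weekly 50-min sessions of" the intervention over 6 months.
- **Contact, wait-list arm (Wait-list control group).** Participants "will be contacted again after 6 months for post-assessment". At that point "participants in this condition are asked to provide information on any inpatient or outpatient treatment they have received and on major events" that they think affected their symptoms. No matching enquiry is described for the intervention arm. Its post-intervention questionnaire is described as covering satisfaction and suggestions (Feasibility and acceptability measures; supplement S3 is not shown).
- **Use of the count.** The Background gives the aim as "acceptability (i.e., drop-out rate, number of adverse events" and satisfaction. Feasibility and acceptability measures lists the count as an outcome, and the Analysis plan summarises acceptability descriptively in the intention-to-treat population.

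**The concern.** When an event enters the record only because someone mentions it, the number recorded depends on how often there is someone to mention it to. Here that opportunity is tied to the randomised arm. A count in the intention-to-treat population then joins one arm seen weekly with one for which no contact is described until the end.

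The likely direction is under-counting on the wait-list, partly offset by the enquiry made only there. If the report sets the two counts side by side, a higher number under therapy could reflect harm or merely more chances to report it. Symptom exacerbation counts as an adverse event, and the wait-list arm is the natural source of its background rate. Events that nobody asked about cannot be recovered by later analysis.

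**Working it through.** The plan states no adverse event rate or contrast, so there is no figure to reproduce.

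**1. Described contacts after baseline.** Between t0 and t1: up to 24 (intervention) against 0 described (wait-list). Including t1: 24 + 1 = 25 against 1.

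**2. What other data already catch.**
- Changes in medication, occupation, living situation and adjunct treatment are recorded between t0 and t1, with no restriction to one arm (Additional measures).
- Worsening that lasts to t1 shows on scales used in both arms at t0 and t1: BNSS, RFS, GAF, WEMWBS, CDSS and PSYRATS.
- Wait-list hospital stays are partly recoverable from the question on inpatient treatment.

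What remains is mainly transient, non-serious events that led to no change in care and are not captured by those scales.

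**3. Illustration of the distortion (assumed inputs).** Let the true probability p of at least one event be equal in both arms, with 15 per arm. Assume detection of 0.95 under therapy and d on the wait-list. Recorded ratio = 0.95/d. Spurious risk difference = p × (0.95 − d). Expected participants recorded = 15 × p × detection. At p = 0.30 the intervention arm records 15 × 0.30 × 0.95 = 4.3.

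| d | Ratio | Wait-list recorded | Spurious difference |
|---|---|---|---|
| 0.75 | 1.27 | 3.4 | 0.06 |
| 0.50 | 1.9 | 2.3 | 0.135 |
| 0.25 | 3.8 | 1.1 | 0.21 |

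Over p from 0.20 to 0.50 and the same d, the spurious difference runs from 0.20 × 0.20 = 0.04 to 0.50 × 0.70 = 0.35. Nothing in the article says which row is closest.

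**4. Reach of a change at t1.** Under Sample size, "the target for this feasibility study was set at" 30. Trial status reports 22 included, 10 intervention and 12 wait-list.
- Still to recruit: 30 − 22 = 8, and 8/30 = 27%.
- If the arms finish at 15:15: 15 − 10 = 5 intervention and 15 − 12 = 3 wait-list.
- Those of the 22 who have not reached t1 would be added; their number is not stated.

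**5. What so few answers can show.** With no events among n participants, the exact two-sided 95% upper limit is 1 − 0.025^(1/n):
- n = 3: 71%
- n = 5: 52%
- n = 15: 22%

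With 5 and 3 participants, prompted answers can be listed but not compared.

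**The case against.** The strongest reply is that the protocol never makes the comparison in question. Acceptability is descriptive, and no between-arm test of adverse events is announced. Causality is reviewed case by case, and the 30% stopping rule counts only events attributed to the intervention, so neither needs a wait-list count. This stands. A reader might infer that a planned safety contrast is biased or that the stopping rule fails; the article supports neither.

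Second, zero wait-list contact is what the article describes, not what is known to happen. It condenses a fuller protocol. Table 1 (the schedule) and Fig. 1 (the flow diagram) are not shown and could contain an adverse event item or a contact. Changes in care are said to be recorded throughout, and the trial manager keeps a running tally of events. This also stands: one cannot conclude that wait-list participants go unobserved for 6 months. Yet neither statement gives a contact schedule or a structured enquiry, and the rule that is written down is spontaneous report.

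Third, a single question at t1 is weakest for the very events that remain, because minor transient symptoms over 6 months are poorly recalled, and it changes ascertainment mid-trial for few participants. This is fair. It argues against inference from the answers, but not against asking both arms the same thing.

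**Conclusion.** The point holds as a limited, inexpensive improvement and not as an error in a planned analysis. Followed as written, the capture rule ascertains a named acceptability outcome unequally by arm, mainly for transient, non-serious events. The described imbalance is up to 24 contacts against 0 before t1. How many events are missed is unknown, and the ratios of 1.27 to 3.8 above rest wholly on assumed detection probabilities.

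The conclusion assumes that the unseen schedule and flow diagram add no common adverse event enquiry; if they do, the point largely falls away. Whether the progression criteria use the count is also unknown, because Table 2 is not shown. The remaining risk is one of reading: two counts that look comparable and are not.

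**What to change.** At every remaining t1 interview, put the wait-list questions on treatment and major events, plus one brief adverse event question, to both arms. Ask them after the symptom ratings and cut them from the video. The blinding section already provides for this, since sequences that could reveal "allocation or point of assessment are deleted before the secondary rating".

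In the report:
- list prompted and spontaneous events separately by arm;
- give the number of participants who were asked the prompted questions;
- state that spontaneous counts are not comparable between arms;
- draw no by-arm inference from the few prompted participants;
- note that those already past t1 lack the prompted data and that 6-month recall is imperfect.

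The cost is a few questions in an existing interview, a change of protocol wording and possibly an ethics amendment. Coverage is partial because recruitment is well advanced. If the questions are judged not worth adding this late, the non-comparability statement alone costs nothing and prevents the misreading.

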### Outcomes

#### Feasibility and acceptability measures

To assess feasibility of “Goals in Focus” and trial procedures, the following data is collected: (1) referrals (number of participants referred to the study), (2) eligibility rates (proportion of enrolled participants found eligible), (3) number of participants consenting to study participation and reasons for refusals, (4) retention rate (i.e., number and proportion of participants who attend *t*_1_ assessment and completeness of data at *t*_1_), (5) attendance rates and dose of intervention (i.e., number of sessions delivered within 6 months), (6) data attrition (proportion of outcome data not obtained), and (7) treatment adherence as indicated by the therapists’ self-report in the post-treatment questionnaire.

Acceptability is assessed by (1) drop-out rate (i.e., number of withdrawals), (2) number of adverse events, (3) participants’ satisfaction with treatment and personal outcomes and suggestions for improvement as indicated by each participants’ response to three quantitative and three qualitative questions (see post-intervention questionnaire, supplement S 3; e.g., participants are asked to indicate how helpful they perceived “Goals in Focus” to be for their problems and for approaching their goals and to suggest improvements), and (4) therapists’ satisfaction as measured by the post-intervention questionnaire, therapist version (see supplement S 4).

Progression criteria for a subsequent trial were set according to existing recommendations for feasibility studies [79, 80] and can be found in Table 2.

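### One adverse-event category, the newly detected condition, starts at intervention administration, so before t1 it can be met in the therapy arm but not on the wait list

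*Protocol article*

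**What the plan says.** The Safety reporting section gives two consecutive statements of what an AE is.

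- **The opening rule.** It concerns unfavourable symptoms that are spontaneously reported. A "symptom that develops or deteriorates during the study will be classified as an adverse event (AE), whether or not it is considered to be related", so causality plays no part at this step. The period is the study, so the rule covers both arms.
- **The list.** It has four categories. Two have no starting point: "AEs comprise exacerbation of pre-existing symptoms, increase in frequency or intensity of a pre-existing episodic event or condition". Two start at treatment: a "condition that is detected after trial intervention administration", and a persistent illness or "symptom present at baseline that expectedly or unexpectedly worsens following administration of the intervention".

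Under Wait-list control group, participants in that arm "will be contacted again after 6 months for post-assessment and then offered the" intervention. Under Feasibility and acceptability measures, the acceptability outcomes include "2) number of adverse events". The Analysis plan describes feasibility and acceptability in the intention-to-treat population, which contains both randomised arms.

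**The concern.** The two statements use different starting points. The opening rule runs over the study for everyone, while half of the list begins when the intervention is given. Between baseline and t1 only one arm receives it, and the article names no equivalent starting point, such as randomisation, for the other.

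The AE count is a named acceptability outcome, and the Discussion makes the larger trial conditional on the intervention proving safe, feasible and acceptable. The wait-list arm is the only randomised indication of how many events occur without therapy. If the same event is an AE in one arm and not in the other, the two counts do not measure the same thing. The trial manager reviews and tracks events and no data monitoring committee is convened, so consistent counting depends largely on the written definition.

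**Working it through.** The article states no AE rate or expected count, so there is no figure to reproduce. The check sets the sentences side by side for events before t1 (in the therapy arm, after the first session).

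| Event | Therapy arm | Wait list, list read as complete | Wait list, both sentences applied |
|---|---|---|---|
| New condition, volunteered by the participant as a symptom | AE | Not an AE | AE |
| New condition, detected by staff and not volunteered | AE | Not an AE | Not an AE |
| Worsening of something present at baseline | AE | Largely an AE, through the unanchored categories | Largely an AE |

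1. **Row 1.** The opening rule makes this an AE in either arm. It is lost on the wait list only if the list is taken as the full content of the definition.
2. **Row 2.** The opening rule requires spontaneous reporting, so it does not apply. The therapy-arm event enters through the list. The wait-list event cannot, because there has been no administration. This difference remains under either reading. It is also a practical possibility: the t1 assessment in both arms includes clinical interviews (for example for depression and positive symptoms), which can elicit something the participant has not volunteered.
3. **Row 3.** The anchored wording ("present at baseline that expectedly or unexpectedly worsens following administration of the intervention") overlaps with the two unanchored categories, so most such events can be counted on the wait list. A difference remains only if the anchored category is taken to be the sole route for persistent illness.

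**Form of the gap.** Let p be the expected number of new conditions per participant before t1, the same in both arms and equally well detected. Let q be the share that staff detect but participants do not volunteer. With the planned 15 per arm, the difference created by the definition alone is:

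- list read as complete: 15 × p
- both sentences applied: 15 × p × q

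Neither p nor q is given. Purely as an assumption, p = 0.1, 0.2 and 0.3 give 15 × p = 1.5, 3 and 4.5 events. Under the joint reading the gap lies between 0 (q = 0) and those values (q = 1). Where it operates, it adds to the therapy-arm count relative to the wait list.

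**The case against.** The strongest reply is that the opening rule is mandatory and arm-neutral, and that the list merely elaborates it. Nothing in the list says that only these categories count. On that reading, spontaneously reported new symptoms on the wait list are AEs and most of the difference disappears. This is a fair reading and it stands for row 1. It does not remove row 2, because the opening rule is limited to spontaneous reports.

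Several stronger inferences are tempting, and the article does not support them.

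- **A two-fold excess of AEs in the therapy arm.** Assuming rates of 20% for new conditions and 20% for exacerbations, the complete-list reading gives 15 × (0.2 + 0.2) = 6 against 15 × 0.2 = 3. With 10% and 30% it is 6 against 4.5; with 30% and 10%, 6 against 1.5. These rates are invented, and the result simply removes new conditions from one arm. It is no evidence that the list is meant to be complete.
- **Worsening illness is uncountable on the wait list.** The unanchored categories largely cover it.
- **A biased between-arm test.** None is stated. Acceptability is to be described, and separate reporting by arm is specified only for clinical outcomes.
- **An effect on stopping or progression.** The 30% rule uses AEs attributable to Goals in Focus, so uncounted wait-list events do not enter it. The progression criteria table is not reproduced in the text available, so nothing can be said about it.

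**Conclusion.** The concern holds in a limited form. The AE definition has two reference points, and for newly detected conditions the second cannot be met on the wait list before t1. If the list is complete, all new conditions in that arm are excluded. If the sentences are read together, only those detected by staff and not spontaneously reported are excluded. Some dependence on arm therefore remains under either reading, provided such events occur. For worsening illness the problem is small.

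The consequence is confined to the descriptive AE count by arm. Its size cannot be derived from the article. This is an inconsistency in a definition that the article states itself, so it is not a detail left to a fuller document. It is a modest point in a 30-person feasibility trial, but worth correcting because the remedy is a change of wording.

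**What to change.** Replace both intervention-based starting points in the list with one window that is the same for everyone: after randomisation, in either arm. For the by-arm count, close the window at t1, since wait-list participants may start the intervention after that. Keep relatedness to the intervention as a separate causality judgement, as the section already provides. State that AE counts will be reported by arm on this single definition.

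The cost is a change to the wording of the definition and, where it repeats that wording, the recording form. The wait-list AE count may rise. With 22 participants already included when the article was written, events recorded so far should be reclassified under the new wording in both arms. Wait-list conditions that were noticed but not recorded as AEs may not be recoverable, and the report should say so.
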